## Discussion

### Changes to the protocol after commencement of recruitment in April 2003

Based on the experience of the pilot phase, it became apparent that our projection that 40% of eligible women would consent to participate on the basis of a mailed invitation was optimistic. A number of additional strategies which aimed to increase participation were implemented from mid 2003 onwards. These included: (i) research team members regularly attending booking clinics at two study hospitals, and 'early-bird' prenatal education classes at a third hospital (which did not have a booking clinic), in order to foreshadow the invitation to take part in the study and answer any questions women had regarding participation; (ii) inclusion of a study leaflet containing a brief outline of the study in the information packages sent to women by participating hospitals prior to their first antenatal visit; (iii) mailing information about the study to general practitioners and specialist obstetricians who provide shared care at participating hospitals and asking them to display materials about the study in waiting areas. We also regularly met with midwives at participating hospitals and produced a six-monthly newsletter to provide information for clinical staff about the study, and ensure that they knew how to contact the research team throughout the period of recruitment. We ruled out adding a second mailed reminder, as we did not want to place women under pressure to participate given the long term nature of follow-up and sensitive nature of some issues covered in questionnaires and interviews.

Our original aim had been to complete recruitment over a 20–24 month period. One of the participating hospitals ceased bookings for maternity care from early 2004. A new hospital within the same network opened in late 2004; we obtained approval to commence recruiting women from this hospital in June 2005. This affected our recruitment to a minor extent. Ultimately recruitment was completed over a two and a half year period, April 2003- December 2005.

### Strengths and limitations of the study

Features of the study which distinguish it from prior research include: the capacity to identify incident cases of morbidity and clustering of health problems; a large enough sample to detect clinically important differences in maternal health outcomes associated with the method of birth; careful exposure measurement involving manual abstraction of data from medical records in order to explore mediating factors and possible causal pathways; and use of a variety of strategies to improve ascertainment of health outcomes such as faecal incontinence, perineal pain and sexual health issues. The latter include use of standardised instruments and questions already tested in prior research with re-piloting to assess acceptability and validity for Victorian women and comparison of results from self-administered questionnaires and telephone interviews.

The rationale for restricting eligibility to women who have reached a minimum of 10 weeks gestation was to limit the number of women enrolling in the study who subsequently experience an early pregnancy loss (spontaneous or induced abortion). Restricting eligibility at enrolment to women who are ≤20 weeks gestation was intended to ensure that data on health status in early pregnancy are available for the whole cohort. A second rationale is to limit the potential for recall bias affecting responses to questions concerning pre-pregnancy health status. A conception cohort would be a more robust design for collection of information on symptoms prior to pregnancy, but in practice is difficult to achieve. The Longitudinal Study of Australian Women (Women's Health Australia) which includes a cohort of younger women recruited at age 18–23 years in 1996, who have now been followed up on two occasions since 1996, has not been designed to facilitate identification of women in the early stages of pregnancy and/or at the time of giving birth [25]. The difficulty and costs of keeping track of a necessarily very large cohort and facilitating follow-up of a sub-sample who become pregnant present major obstacles in designing a study with a capacity to collect information from women immediately preceding and after conception.

The fact that recruitment to the study has been lower than anticipated means that there is increased potential for selection bias related to our primary outcomes. Detailed information on medical conditions, surgical procedures, and symptoms prior to pregnancy has been collected in the baseline questionnaire. Women who report medical conditions, such as Crohn's disease, ulcerative colitis or chronic renal disease that may predispose women to primary outcomes being assessed in the study will be excluded from analyses assessing obstetric risk factors. We will also compare the prevalence of prior medical conditions and symptoms reported by study participants with data from community prevalence studies with respect to urinary and bowel symptoms as a check for evidence of selection bias.

Exclusion of women first attending for pregnancy care at >20 weeks gestation is expected to have a minor impact on the representativeness of the sample. A population-based study conducted by the Victorian Perinatal Data Collection Unit (VPDCU) in 1998 showed that 81.5% of women have their first antenatal visit in the first trimester, and less than 10% attend for a first visit later than 20 weeks [32]. Exclusion of women with insufficient fluency in English to complete written questionnaires and telephone interviews is likely to have greater impact on the representativeness of the sample as approximately 40% of women giving birth at the two tertiary level hospitals during the study period were born overseas in countries where English is not the first language. The restriction of recruitment to women attending public hospitals is a further limitation, especially as it is plausible that differences in the way that care is managed in the private sector (e.g. greater likelihood that labour will be induced and/or augmented, and a higher proportion of women giving birth by caesarean section) may have an impact on maternal health outcomes. Funding constraints and issues of feasibility prevented us from extending the study to these groups.

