**Methods/design:**

The Maternal Health Study is a longitudinal study designed to fill in some of the gaps in current research evidence regarding women's physical and psychological health and recovery after childbirth. A prospective pregnancy cohort of >1500 nulliparous women has been recruited in early pregnancy at six metropolitan public hospitals in Melbourne, Australia between April 2003 and December 2005. In the first phase of the study participants are being followed up at 30–32 weeks gestation in pregnancy, and at three, six, nine, 12 and 18 months postpartum using a combination of self-administered questionnaires and telephone interviews. Women consenting to extended follow-up (phase 2) will be followed up six and 12 months after any subsequent births and when their first child is four years old. Study instruments incorporate assessment of the frequency and severity of urinary and bowel symptoms, sexual health issues, perineal and abdominal pain, depression and intimate partner violence. Pregnancy and birth outcome data will be obtained by review of hospital case notes.

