### Sample size

Sample size calculations were conducted using Epi Info Version 5 based on prevalence estimates for primary outcomes derived from a population-based Victorian survey of recent mothers [16]. Table 1 shows power calculations for the study with alpha of 0.5 and beta of 0.20, assuming ratios of:

**Table 1 T1:** Sample size calculations

**Exposure comparison (ratio of unexposed: exposed)**	**Outcome of interest**	**Difference**	**Sample size estimate**	**Total number required***
**Spontaneous vaginal birth:forceps/vacuum extraction (2:1)**	Urinary incontinence Faecal incontinence Sexual problems Perineal pain	11% versus 18% 2.6% versus 8% 24% versus39% 20% versus 53%	930 642 360 168	1200 800 450 210
**Emergency caesarean:forceps/vacuum extraction (1:2)**	Urinary incontinence Faecal incontinence Sexual problems	7% versus 18% 3.9% versus 10.5% 29% versus 39%	371 573 841	950 1500 2200
**Elective caesarean:forceps/vacuum extraction (1:5)**	Urinary incontinence Faecal incontinence Sexual problems	2.4% versus 18% 2.8% versus 10.5% 27% versus 39%	276 763 938	900 2500 3100

* Taking into account the relative frequency of different methods of delivery

• 2:1 (unexposed:exposed) for comparison of spontaneous vaginal births with operative vaginal births;

• 1:2 for comparison of emergency caesarean sections with operative vaginal births; and

• 1:5 for comparison of elective caesarean sections with operative vaginal births.

These ratios were based on routinely collected data for women giving birth in Victoria in 1999. Since the five study hospitals are all public hospitals and nulliparity was an eligibility criterion for the study, the ratios were calculated based on confinements of women admitted as public patients for the birth of their first child.

Using these parameters and allowing for 20% loss to follow-up by 18 months postpartum, we estimated that a sample of 1,900 women would be sufficient to test the hypothesis that primiparous women having an operative vaginal birth have a twofold greater relative risk of developing urinary incontinence, faecal incontinence and sexual problems compared with women having a spontaneous vaginal birth, and to detect a relative risk of 2.0 for urinary incontinence for all exposure comparisons.

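### The unqualified claim of a large enough sample is not supported by Table 1 at the achieved enrolment, and the main urinary incontinence comparison has no reserve for the exclusions that the plan itself makes

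*Protocol article*

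**What the plan says.** The Sample size section takes its inputs from existing survey data, "based on prevalence estimates for primary outcomes derived from a population-based Victorian survey of recent mothers", and allows for 20% loss by 18 months. On that basis, "we estimated that a sample of 1,900 women would be sufficient". The statement then lists what 1,900 covers. It names operative versus spontaneous vaginal birth for urinary incontinence, faecal incontinence and sexual problems, and urinary incontinence for every exposure comparison in Table 1.

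The Abstract (Methods/design) reports what was achieved: "A prospective pregnancy cohort of >1500 nulliparous women has been recruited in early pregnancy". The exact count is not given.

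Three other places bear on the number of women analysed:

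- Study hypotheses 1 and 2 concern incident cases, and Analysis considerations plans separate analyses of incident and prevalent morbidity.
- Strengths and limitations says that women with predisposing medical conditions "will be excluded from analyses assessing obstetric risk factors".
- The same section admits that recruitment fell short of expectation, but draws only a selection-bias consequence.

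The claim of "a large enough sample to detect clinically important differences in maternal health outcomes associated with the method of birth" stands in the Abstract (Discussion) and in Strengths and limitations. It carries no limit to outcome or comparison, and power is not recalculated anywhere.

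**The concern.** The adequacy claim describes the study as achieved, but the only calculation behind it describes the study as planned. Two things changed the basis. Fewer women were enrolled than calculated. The hypotheses also need women free of the symptom before birth, whereas the sizing used prevalence among all recent mothers and allowed for loss to follow-up only.

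A reader who takes the claim at face value may treat a null result on incident urinary incontinence, or on a caesarean comparison, as evidence of no effect when the analysis had little chance of showing one. The article lists adequate sample size among its key ethical issues and criticises earlier studies for inadequate power, so its own claim should match its own table.

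**Working it through.** **Inputs.** All from the Sample size section and Table 1 unless stated: power 80%; ratios 2:1, 1:2 and 1:5; the Table 1 rates; 20% loss; 1,900 planned. Recruited: more than 1,500 (Abstract), taken as 1,500. The section prints "alpha of 0.5 and beta of 0.20". An alpha of 0.5 would give about 262 for the first row, whereas two-sided 0.05 reproduces it, so 0.05 is used.

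**Reproducing the plan.** The two-proportion sample size with Fleiss continuity correction, 11% versus 18% at 2:1, gives 930, as stated. Seven other rows agree within 3% by the same method: 644 (stated 642), 360 (360), 372 (371), 843 (841), 276 (276), 744 (763) and 942 (938). Emergency caesarean faecal incontinence (573) gives 567 without correction and 633 with it. Perineal pain gives 84 against 168; that row plays no part here.

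**Retained women.** Planned: 1,900 × 0.8 = 1,520. Achieved: 1,500 × 0.8 = 1,200.

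**Power formula.** Comparison size N = retained women × (Table 1 sample size ÷ Table 1 total), split by the stated ratio into n1 and n2. With d the difference in proportions and p̄ the pooled proportion:

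- s0 = √[p̄(1−p̄)(1/n1+1/n2)]
- s1 = √[p1(1−p1)/n1 + p2(1−p2)/n2]
- c = (1/n1+1/n2)/2
- power = Φ[(d − c − 1.96·s0)/s1], with c = 0 for the uncorrected version

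**Urinary incontinence, operative versus spontaneous, 1,200 retained.** N = 1,200 × 930/1,200 = 930; n1 = 620, n2 = 310; p̄ = 0.1333; s0 = 0.02365; s1 = 0.02518; c = 0.00242.

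- Corrected: (0.07 − 0.00242 − 0.04635)/0.02518 = 0.843, power 80.0%
- Uncorrected: (0.07 − 0.04635)/0.02518 = 0.939, power 82.6%
- At the planned 1,520: 88.5% corrected, 90.1% uncorrected

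**The five named comparisons at 1,200 retained, and after assumed exclusions** (continuity-corrected power, Table 1 risks unchanged):

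| Comparison | Table 1 total | No exclusion | 10% | 20% | 30% |
|---|---|---|---|---|---|
| Urinary, operative v spontaneous | 1,200 | 80.0% | 76% | 70% | 64% |
| Faecal, operative v spontaneous | 800 | 93% | 90% | 87% | 82% |
| Sexual problems, operative v spontaneous | 450 | 99.7% | 99% | 99% | 97% |
| Urinary, emergency caesarean v operative | 950 | 90% | 86% | 81% | 74% |
| Urinary, elective caesarean v operative | 900 | 95% | 91% | 84% | 75% |

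The exclusion shares are an assumed range. Uncorrected, the first row reads 83, 79, 74 and 69%.

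**Reserve in the first row.** At 1,520 the plan could lose 1 − 1,200/1,520 = 21% of women and still meet its requirement. At 1,200 it can lose 1 − 1,200/1,200 = 0%. Recruits needed to keep 1,200 at-risk women after 20% loss are 1,200/(0.8 × 0.9) = 1,667 at 10% exclusion, 1,200/(0.8 × 0.8) = 1,875 at 20%, and 1,200/(0.8 × 0.7) = 2,143 at 30%.

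**Rows outside the named list.** Emergency caesarean versus operative birth for faecal incontinence needs 1,500. The planned 1,520 met that total; 1,200 does not. N = 1,200 × 573/1,500 = 458, power 62.5% corrected and 70.1% uncorrected (75.7% and 81.1% at 1,520). The rows needing 2,200, 2,500 and 3,100 exceed 1,520 as well as 1,200.

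**The case against.** A reader might infer that, because about 1,500 instead of 1,900 were recruited, the powered comparisons have all lost their 80%. The article does not support this. The Sample size section names five comparisons, and the largest total among them is 1,200, which 1,500 recruits with 20% loss just supply. Nor should the low power of the rows needing 2,200, 2,500 and 3,100 be blamed on the shortfall: Table 1 shows openly that 1,900 never covered them, and the sufficiency statement omits them. It also omits faecal incontinence after emergency caesarean.

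Other fair points:

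- The share of women with symptoms before birth is not given, so any figure below 80% for a named comparison rests on an assumption.
- Repeated assessment to 18 months could give cumulative incidence above a one-time prevalence, which would raise power. Lower risks in symptom-free women would reduce it: with both urinary risks cut by 20% and no exclusion, power is 69–73%.
- The 20% loss applies by 18 months, so earlier analyses may keep more women.
- Some planned models use timing of onset as a covariate, so women with earlier symptoms do not leave every analysis.
- More than 1,500 is a lower bound, not a count.

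These points narrow the concern but do not remove it. The claim in the Abstract and in Strengths and limitations names no comparison, so it reaches beyond the five. Hypotheses 1 and 2 are about incident cases, so the restriction applies to the primary questions. Better inputs might restore some reserve, but the article does not show that they do.

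**Conclusion.** The concern holds in a limited form. The adequacy claim is wider than Table 1 supports at the achieved enrolment and should be restated; the design is not thereby invalid.

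- On the shortfall alone, the five named comparisons keep about 80, 93, 99.7, 90 and 95% power (corrected). Faecal incontinence and sexual problems, operative versus spontaneous, stay above 80% even at a 30% exclusion.
- Urinary incontinence, operative versus spontaneous, has lost its whole reserve. With correction, any exclusion takes it below 80%; without correction, a 10% exclusion does.
- Faecal incontinence, emergency caesarean versus operative, moves from covered by its Table 1 total to about 63–70% power. It is the only row that the shortfall alone takes below its requirement.

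These results assume exactly 1,500 recruited, 20% loss, two-sided alpha 0.05, the Table 1 risks and ratios, and an exclusion share of 10–30% that the article does not supply. A higher true count or higher incident risks would improve them.

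**What to change.** 1. State the number recruited, the number retained at each follow-up, and the number free of each symptom before birth and without an excluded medical condition.
2. Recompute power, or the detectable difference, for each Table 1 comparison on those at-risk women. The baseline questionnaire and pregnancy interview already collect the symptom data.
3. In the Abstract and in Strengths and limitations, replace the general claim with the list of comparisons that keep at least 80% power. Present the others as estimates with confidence intervals.
4. Where low recruitment is discussed, add its effect on power to its effect on selection bias.

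The cost is one recalculation, some text, and a less favourable statement of power. No further recruitment or change to data collection is needed.

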### Analysis considerations

A major challenge in planning analyses assessing causal pathways is the extent to which obstetric risk factors are linked, and the associated difficulty in analysis of sorting out the impact of method of birth (as the 'exposure of main interest') from other exposure and treatment effects. Recently there has been much debate about the possible benefits of elective caesarean section in protecting women's pelvic floor and preventing urinary incontinence [9-12]. Although sample size calculations for the study were not based on comparisons of spontaneous vaginal birth with elective caesarean section, the study will have adequate power for this comparison. Additional file 1 (table 2) and 2 (table 3) provide a summary of pregnancy and birth cohort studies which have assessed the role of obstetric factors for urinary incontinence in pregnancy and after childbirth. Most of the included studies with data on operative births report that caesarean section is protective against urinary incontinence after childbirth compared with vaginal birth [see Additional File 1 and Additional File 2]. However, few of these studies incorporate comprehensive assessment of obstetric risk factors. Only half of the included studies obtained information on obstetric events by reviewing medical case notes [34-36,38,42,45,47,49,50,52-54], and two of these studies relied in part on information obtained from computerised records [53,54]. Many studies do not differentiate women who have an emergency caesarean section in labour from those having an elective caesarean section prior to commencement of labour [36,38-40,46,48,51-54]. Less than half include measures of fetal or infant size [34-36,45,47,48,53,54], maternal size (height, pre-pregnancy BMI) [34,36,48,50,52-54], or genital tract trauma [34,45,47-49,52-54], and only a handful of studies include data on use of analgesia and anaesthesia [43,50,52-54], fetal position in labour [35,39,50] or maternal position in second stage [53]. In contrast, duration of second stage labour is commonly collected as a proxy variable for obstructed labour [33-36,39-41,43,48-51,53,54]. Inconsistencies in the way information on length of labour is recorded, and lack of data on other indicators of possible obstructed labour (e.g. position of the fetus, descent of the fetal head) make it difficult to interpret this data.

In summary, the striking features of this literature are: the lack of consistency in the approaches to data collection taken by different research groups, and the limited extent to which variables related to events in labour other than method of birth have been taken into consideration. Many studies included in Tables 2 and 3 also have inadequate study power for examining obstetric risk factors [33-35,40,43-45,48-50].

Two recently published papers by Glazener et al [53] and MacArthur et al [54] drawing on data from a large multi-centre prospective birth cohort are a welcome addition to this literature. Both papers report carefully conducted analyses for incident cases of morbidity considering a broader range of obstetric and maternal risk factors, including maternal age and BMI. Glazener and colleagues focus on primiparous women at three months postpartum distinguishing between women whose incontinence commenced in pregnancy and those who developed symptoms after giving birth to their first child, while MacArthur et al report on persistent incontinence six years after the index birth adjusting for first delivery mode, maternal age at first birth, and parity. One limitation of this study is that identification of incident cases (onset of symptoms in pregnancy or after birth) is reliant on maternal recall at three months postpartum.

In the Maternal Health Study the baseline survey completed in early pregnancy includes detailed questions regarding urinary and other symptoms: (i) 'at any stage in your life before the current pregnancy' and (ii) in the twelve months prior to the pregnancy. We have also asked separately about childhood enuresis and relevant medical conditions and prior surgery. Detailed information on a comprehensive list of obstetric covariates is being collected from hospital medical records and will be supplemented by women's own accounts of events in labour and birth collected in the questionnaire completed at three months postpartum (Q2). This will enable us to look at variables that are poorly recorded or not available in medical records. For example, we have included questions in Q2 regarding maternal position and method of pushing in active second stage labour. We are also endeavouring to collect information from medical records regarding the timing of events in labour, for example, time of administration of epidural or spinal analgesia/anaesthesia and time that women commenced pushing in second stage labour. Precise definitions have been developed and pilot tested for all obstetric data items being collected from medical records and Q2.

The first step in analysis will be to assess data quality to identify variables that are poorly or inconsistently recorded in medical records and/or women's accounts of labour and birth events. One aspect of this will be to assess the extent of agreement between data collected in self-administered questionnaires and information abstracted from hospital medical records for pregnancy and birth events.

Figure 2 provides a schematic overview of key covariates that will be considered in analysis. The arrows represent possible causal associations between covariates based on available epidemiological evidence regarding obstetric risk factors for maternal morbidity. Planning analyses using causal acyclic diagrams has been advocated by Greenland and others as a useful strategy for identifying variables that may mediate or moderate the relationship between an exposure of main interest and primary health outcome/s [55,56]. Figure 2 illustrates the complexity of possible causal pathways and relationships between obstetric risk factors for maternal morbidity. Considering our hypothesis that vaginal birth assisted by forceps or vacuum extraction is an 'independent' risk factor for urinary incontinence, the diagram illustrates the multiple covariates and combinations of covariates preceding the delivery and subsequent to delivery that may mediate the relationship between the mode of birth and the outcome of urinary incontinence. To take one example, the estimated size of the fetus as large for gestational age might lead directly to the decision to conduct an elective caesarean section, or alternatively, via a range of possible pathways to obstruction in second stage labour and a vaginal birth assisted by forceps or vacuum extraction or an emergency caesarean section. A number of other factors may influence the outcome, including the position of the fetus in second stage labour, length of time in active second stage, whether or not an episiotomy is cut and the extent of other genital tract trauma. The conventional statistical approach – used by many researchers – of adjusting for those covariates such as infant size for which data are available is likely to lead to erroneous conclusions. This is not only because data are rarely available for the full range of covariates illustrated in Figure 2, but also because such analyses fail to consider the complex range of possible pathways involved. Simple adjustment for fetal size assumes that the impact will be the same irrespective of other aspects of labour and birth. Biologically this seems somewhat implausible given the extra pressure on the pelvic floor associated with a long labour and large baby often in occipito-posterior position. While these other factors can also be adjusted for in analysis, it may be more useful to conduct separate analyses restricted to women who do and do not experience labour. This is likely to yield less biased estimates of effect for specific causal pathways [57]. The timing of onset of symptoms (and symptom resolution) presents further challenges in analysis. Separate stratified analyses will be performed for incident and prevalent cases of morbidity.

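### The claim of adequate power for spontaneous vaginal birth versus elective caesarean is not supported for urinary incontinence by the article's own rates, ratios and loss allowance

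*Protocol article*

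**What the plan says.** The Analysis considerations section introduces the debate on whether elective caesarean protects the pelvic floor and prevents urinary incontinence. It concedes that the sample size calculations did not cover spontaneous vaginal birth versus elective caesarean, and then states that "the study will have adequate power for this comparison". No event rate, group size or power accompanies the statement.

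The inputs for checking it are in the Sample size section:

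- Delivery mix: two spontaneous births for each operative vaginal birth, one emergency caesarean for every two operative vaginal births and, for the smallest group, "1:5 for comparison of elective caesarean sections with operative vaginal births". These are based on 1999 Victorian data for first births to public patients.
- Table 1 rates for spontaneous against operative vaginal birth: "11% versus 18% 2.6% versus 8% 24% versus39% 20% versus 53" per cent (urinary incontinence, faecal incontinence, sexual problems, perineal pain).
- Table 1 rates for elective caesarean against operative vaginal birth: "2.4% versus 18% 2.8% versus 10.5% 27% versus 39" per cent (urinary incontinence, faecal incontinence, sexual problems).
- Planned size: 1,900 women, "allowing for 20% loss to follow-up by 18 months postpartum".

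The Abstract reports that more than 1,500 women were recruited. The Strengths and limitations section acknowledges that recruitment fell short of expectation.

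**The concern.** Elective caesarean is the rarest of the four delivery groups, and Table 1 already shows that it limits what the study can detect. Against operative vaginal birth, where the differences are larger, faecal incontinence and sexual problems need 2,500 and 3,100 women in total, both beyond the planned 1,900. A bare statement of adequacy for a contrast that uses this group needs figures behind it, and it is made after recruitment had closed below target.

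The article itself calls the question topical, and it lists adequate sample size among its key ethical issues and its distinguishing strengths. If the power is well below 80%, readers told that it is adequate may take a non-significant result from some 65 to 80 women with elective caesarean as evidence that there is no protective effect.

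**Working it through.** **1. Identify the article's method.** The text gives "power calculations for the study with alpha of 0.5 and beta of 0.20". An alpha of 0.5 does not reproduce Table 1. The Fleiss formula with continuity correction, two-sided alpha 0.05 and 80% power does. With group 1 of size n, group 2 of size r·n, d = |p1 − p2| and p̄ = (p1 + r·p2)/(1 + r):

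- n = [1.96·√((r+1)·p̄(1−p̄)) + 0.842·√(r·p1(1−p1) + p2(1−p2))]² / (r·d²)
- corrected n = (n/4)·[1 + √(1 + 2(r+1)/(n·r·d))]²

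For elective caesarean versus forceps/vacuum, urinary incontinence (2.4% vs 18%, r = 5): n = 38.6, corrected 45.9, rounded up to 46; 46 × 6 = **276**, and Table 1 states 276. Spontaneous versus operative birth (11% vs 18%) gives 930, and Table 1 states 930. Eight of the ten rows agree within 3%. The exceptions are perineal pain (84 computed, 168 stated) and faecal incontinence for emergency caesarean (633 computed, 573 stated).

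**2. Group shares.** Setting operative vaginal birth to 1, the ratios give spontaneous : operative : emergency : elective = 2 : 1 : 0.5 : 0.2, which sums to 3.7.

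- Spontaneous: 2/3.7 = 54.1%
- Elective: 0.2/3.7 = 5.4%
- Spontaneous to elective: 10:1

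**3. Size needed for 11% vs 2.4% at 10:1.** p̄ = (0.024 + 10 × 0.11)/11 = 0.1022 and d = 0.086.

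- Uncorrected: n = (1.969 + 0.485)²/(10 × 0.086²) = 81.4 elective; × 11 = 896; ÷ (2.2/3.7) = about 1,506 women.
- Corrected: n = 93.8 elective; × 11 = 1,032; ÷ (2.2/3.7) = about **1,735 women with complete data**.

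Rounding the groups up to whole women moves these totals only slightly, to 1,517 and 1,739.

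**4. Size available.** Planned: 1,900 × 0.8 = 1,520. Achieved, taking more than 1,500 as 1,500: 1,500 × 0.8 = 1,200, which gives 0.541 × 1,200 = 649 spontaneous and 0.054 × 1,200 = 65 elective.

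**5. Power for urinary incontinence.** Formula: Φ[(d − c − 1.96·s0)/s1], where s0 is the pooled standard error, s1 the unpooled one, and c = ½(1/n1 + 1/n2) if corrected, otherwise 0. At 649 vs 65, s0 = 0.0394, s1 = 0.0226 and c = 0.0085:

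- Uncorrected: Φ[(0.086 − 0.0772)/0.0226] = Φ(0.39) = 65%
- Corrected: Φ(0.01) = about 50% (49% when the sample size formula is inverted)

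| Analysed (spontaneous vs elective) | Corrected formula | Exact Yates | Uncorrected formula | Exact chi-square |
|---|---|---|---|---|
| 1,500 less 20% (649 vs 65) | 49-50% | 55% | 65% | 69% |
| 1,500, no loss (811 vs 81) | 69% | 73% | 80% | 82% |
| 1,900 less 20% (822 vs 82) | 70% | 73% | 80% | 82% |

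Table 1's last column implies a slightly smaller operative share (about 25.7% rather than 27.0%). With that share, power at 1,200 analysed is 45% corrected and 62% uncorrected.

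**6. Other outcomes.** Table 1 gives 2.6% vs 2.8% for faecal incontinence and 24% vs 27% for sexual problems, so almost no difference is expected between these two groups. It gives no elective caesarean rate for perineal pain.

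**The case against.** The case for the sentence has substance, and several parts of it stand.

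- **Planned size.** Without continuity correction the requirement (about 1,506) falls just under the planned 1,520, so the claim could have been fair for the original plan. This stands, but the sentence was written after recruitment ended at just over 1,500.
- **Loss.** The 20% is the allowance at 18 months. Outcomes are also collected from three months on, and repeated-measures models are planned. Power at earlier visits may be higher, up to the no-loss row. The article gives no loss figures for those visits.
- **Choice of test.** The planned analysis is stratified and logistic regression, and the Yates test is conservative: at 649 vs 65 with both rates at 10% its true size is about 2.8%. An unadjusted logistic likelihood-ratio test has about 80% power at 649 vs 65 (true size about 5.4%), whereas the Wald test has about 32%. Power with so few expected events therefore depends heavily on the test, and no single replacement figure is established.
- **Delivery mix.** The 5.4% share rests on 1999 ratios, while births followed recruitment in 2003-2005. At 1,200 analysed with 54.1% spontaneous births, a 7% elective share gives 80% uncorrected and 70% corrected; 8% gives 87% and 79%.

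A reader might also infer more than the document supports. One inference is that the study is badly undersized for faecal incontinence and sexual problems because power there is about 10% or less. The surrounding text concerns urinary incontinence, and low power against near-equal expected rates says little about sample size. Another is that restriction to incident cases must lower power further. It reduces numbers but also changes both rates, and the article gives no figures. A third is that the investigators intend to conclude no difference; nothing in the article says so.

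**Conclusion.** The concern holds for urinary incontinence. Under the article's own rates, ratios, loss allowance and sample size method, power at the achieved size is about 50-55%; without the continuity correction it is 65-69%. The two-proportion calculations reach about 80% only by dropping the correction and also assuming either no loss or the full planned 1,520 analysed.

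This rests on two-sided alpha 0.05 (assumed, since the printed 0.5 does not fit Table 1), exactly 1,500 recruited, 20% loss and the 1999 delivery mix. A larger elective share or a likelihood-ratio test would raise the figure, and a Wald test would lower it. The finding is that the unqualified claim lacks support, not that one particular power value is proven.

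It should be fixed but is not critical. The contrast appears in none of the nine pre-specified hypotheses, and the article openly says the sample size was not based on it.

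**What to change.** Either delete the adequacy sentence or replace it with:

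- the power for urinary incontinence at the achieved size, given as a range, with the assumptions named (11% vs 2.4%, the 1999 delivery mix, 20% loss, two-sided alpha 0.05, the test used);
- an undertaking to update the figure once the actual number of elective caesareans is known;
- a statement that the claim does not extend to faecal incontinence or sexual problems, where Table 1 expects almost no difference;
- a statement that the contrast will be reported as an estimate with a 95% confidence interval.

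The cost is a sentence or two of text and a less favourable claim. Design, data collection and the planned models are unaffected.
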